## Abstract

**Background:**

This project studies the effect of group-based Acceptance and Commitment Therapy (ACT) following Attention Bias Modification (ABM) on residual symptoms in recurrent depression. ACT is a cognitive-behavioral intervention combining acceptance and mindfulness processes with commitment and behavior-change processes. ACT enjoys modest empirical support in treating depression and has also shown promising results in secondary prevention of depression. The experimental cognitive bias modification (ABM) procedure has been shown to reduce surrogate markers of depression vulnerability in patients in remission from depression. The aim of the current project is to investigate if the effect of group-based ACT on reducing residual depressive symptoms can be enhanced by preceding it with ABM. Also, assessment of the relationship between conceptually relevant therapeutic processes and outcome will be investigated.

**Methods/design:**

An invitation to participate in this project was extended to 120 individuals within a larger sample who had just completed a separate randomized, multisite, clinical trial (referred to hereafter as Phase 1) in which they received either ABM (*n* = 60) or a control condition without bias modification (*n* = 60). This larger Phase-1 sample consisted of 220 persons with a history of at least two episodes of major depression who were currently in remission or not fulfilling the criteria of major depression. After its inclusion, Phase-1 participants from the Sørlandet site (*n* = 120) were also recruited for this study in which they received an 8-week group-based ACT intervention. Measures will be taken immediately after Phase 1, 1 month, 2 months, 6 months, and 1 year after the conclusion of Phase 1.

**Discussion:**

This study sequentially combines acceptable, nondrug interventions from neuropsychology and cognitive-behavioral psychology in treating residual symptoms in depression. The results will provide information about the effectiveness of treatment and on mechanisms and processes of change that may be valuable in understanding and further developing ABM and ACT, combined and alone.

**Trial registration:**

ClinicalTrials.gov, Identifier: NCT02648165. Registered on 6 January 2016.

**Electronic supplementary material:**

The online version of this article (10.1186/s13063-018-2515-9) contains supplementary material, which is available to authorized users.

## Background

Depression is a condition that affects many individuals in adverse ways. The World Health Organization Global Burden of Disease Study ranked depression as the single most burdensome disease in the world in terms of total disability-adjusted years among people in the middle years of life [1]. Although many new approaches to treating depression have been developed, efficacy for both pharmacological [2] and psychological interventions [3] is still unsatisfying.

Depression is also a highly recurrent disorder. More than 75% of patients diagnosed with major depressive disorder (MDD) experience more than one episode, often relapsing within 2 years of recovery [4]. National Institute of Health and Clinical Excellence [5] has identified secondary prevention as a key goal in the long-term management of depression. Its high recurrence rate suggests specific vulnerability factors that increase risk for developing repeated episodes of MDD. Preventive strategies that identify and ameliorate these factors ostensibly could reduce risk of subsequent episodes [6].

To achieve a comprehensive understanding of the phenomena of depression and its efficacious treatment, multiple perspectives and angles may be necessary [7]. In a recent article, Beck and Bredemeier [7] proposed a more unified model of depression, integrating clinical, cognitive, biological and evolutionary perspectives for treating and preventing depression. Consistent with this recommendation, this project evaluates the impact in reducing residual symptoms in depression of group-based Acceptance and Commitment Therapy (ACT) following Attention Bias Modification (ABM). ACT has been recognized as an efficacious treatment for depression and has also shown promising results in the secondary prevention of depression (e.g., [8–12]). The experimental cognitive bias modification (ABM) procedure has been shown to reduce surrogate markers of depression vulnerability in patients in remission from depression [13].

The current project is an offshoot of a larger randomized controlled, double-blinded clinical trial (i.e., Phase 1) with an outpatient population with a history of depression (NCT02658682). The original NCT investigated symptom changes after 2 weeks of ABM training. The current trial will investigate the effect on reducing residual symptoms in depression of preceding group- based ACT with ABM.

### Attention Bias Modification

The cognitive model of depression is an empirically based framework for identifying and understanding factors that maintain an episode of depression [14].

Within this model, biased attention is believed to play a key role in maintaining depression by fuelling negative thoughts and feelings. Such effects have been shown using a dot-probe paradigm where participants are presented with pairs of stimuli, typically words or faces, consisting of one neutral stimulus and one emotional stimulus. After the offset of each pair, a dot probe appears in the location of either the neutral or the emotional stimulus with allocation of attention measured by latency in detecting it. Participants orienting selectively toward the emotional stimulus will be faster to detect dot probes that replace that stimulus (where they are already attending) and slower to detect probes that replace the neutral stimulus. For example, it has been demonstrated that clinically depressed subjects orient attention toward sad faces rather than neutral or positive faces [15]. A bias towards sad faces has also been reported in previously depressed, currently euthymic subjects [16], and in never-depressed individuals at high risk because of a family history [17]. In our own research group we have shown similar effects in healthy subjects at genetic risk [18]. Together these results suggest that negative cognitive biases may constitute important vulnerability factors for depression, rather than simple markers of lowered mood.

#### The Attentional Bias Modification procedure

Selective biases in attention can be modified by a simple computerized technique; the Attention Bias Modification task (ABM), pioneered by Colin MacLeod et al. [19], was originally developed to test the critical hypothesis that attention bias towards negative emotional information plays a causal role in depression and anxiety [19]. The current approach uses a variant of the dot-probe task, which encourages patients to orient attention towards positive rather than negative stimuli, through an implicit association between the valence of the stimulus and the location of the probe. If the probe appears in the location of the positive stimulus (in 80% of the trials), a habit of automatically directing attention toward positive stimuli is encouraged; i.e., the subject develops a positive attention bias. This manipulation can be compared to a neutral (“placebo”) condition in which the probe appears equally often behind the positive and negative stimuli, without affecting attention bias Fig. 1.

**Fig. 1 Fig1:**
[figure not shown]
Illustration of the dot-probe paradigm. Attentional bias is reflected in faster times to respond to probes presented in the same position as the negative facial expression versus probes located in the opposite position

There has been a growing interest in ABM research [20]. Unfortunately, some projects have been limited by small sample sizes and poor trial methodology [20–23]. While overall findings have been mixed, studies that have found measurable positive changes in emotional biases with ABM, have also reported associated changes in clinical symptoms [13, 24, 25]. For example, a recent small-scale study from the research group of Harmer revealed that alteration of attention bias using the ABM technique causally influenced residual symptoms and the cortisol awakening response [13].

### Acceptance and Commitment Therapy

Acceptance and Commitment Therapy (ACT) is a modern cognitive-behavior therapy that combines acceptance and mindfulness processes, with commitment and behavior-change processes. ACT is a transdiagnostic model that focuses on pathogenic processes that are hypothesized to be common in different forms of human suffering [26]. The main goal in ACT is to foster psychological flexibility, which is defined as “the ability to contact the present moment more fully as a conscious human being and to change, or persist in, behavior when doing so serves valued ends” ([27], p. 7). Psychological flexibility has shown to be associated with higher life satisfaction, emotional well-being, job performance, and job satisfaction [28–31]. Because ACT focuses on promoting psychological flexibility, rather than removing psychopathology, ACT is hypothesized to be well suited for the prevention of psychological disorders [32]. Psychological flexibility, in turn, is strengthened through the six core processes of (1) acceptance, (2) defusion, (3) self as context, (4) committed action, (5) values, and (6) contact with the present moment [32]. Of these six process, acceptance has received the most attention. Correlational and experimental evidence indicates that experiential avoidance, as the converse of acceptance, contributes to the development and maintenance of different psychological and behavioral problems [32]. A basic tenet of ACT is that by nurturing and developing a more accepting and psychologically flexible stance makes it possible to remain in contact with the uncomfortable experiences, while remaining focused on what one wants life to be about both now, and in the future. Another process contributing to psychological flexibility that ACT addresses, that would appear to be of greater relevance for the rationale of this study, is that of present-moment awareness. To somewhat varying degrees and via differing means, ACT protocols seek to strengthen mindfulness in a manner consistent with that of Jon Kabat-Zinn [33] as “paying attention in a particular way: on purpose, in the present moment, nonjudgmentally” (p. 4). Depressed clients are encouraged to “just notice” with an accepting attitude thoughts, emotions, and bodily sensations that might otherwise be responded to in a ruminative and experientially avoidant manner.

#### The ACT model of depression

From an ACT point of view, depression is a secondary emotion that emerges from unsuccessful efforts to experientially control sadness and disappointment as normal and adaptive emotional reactions to distressing life events [26]. In effect, sadness that is not toxic or psychologically unhealthy per se, may be transformed into clinical depression. Rather than targeting changes in the thinking of those who struggle with depression, ACT seeks to change how they respond or relate to their thoughts. For example, thoughts like “I don’t deserve to be loved” may often lead to social isolation. Instead of changing the thought, ACT through mindfulness, acceptance, and defusion strategies seeks to minimize its impact as a barrier to psychological flexibility. In depression there is often a reduction in pleasurable and task-oriented activities [14]. From an ACT perspective, it is not an increase in activity levels by itself that is most important. It is rather exploring and clarifying values, and exemplifying psychological flexibility by committed actions coherent with values in multiple life areas [9]. Consistent with this formulation, Plumb, Hayes, Hildebrandt and Martin [34] found an association between depression and lack of valued action.

### Combining ACT and ABM to reduce the likelihood of recurrence of depression

The overarching hypothesis of this project is that because both ABM and ACT seek to increase attentional flexibility, albeit in differing ways and perhaps to differing degrees, they are likely to complement each other. Accordingly, participants who receive sequentially both treatments generally are expected to demonstrate greater benefits than those who only receive ACT. In a special issue on ABM, Koster and Bernstein suggests that combining ABM and clinical treatment might give a better outcome than “stand-alone” treatment [35].

A positive attentional bias established and maintained through ABM should reduce the degree to which negatively valenced stimuli (whether they be sad faces or unwanted thoughts and feelings) become the focus of present-moment awareness. If successful, ABM, in effect, should thus result in less attentional material that is subject to rumination. However, ABM alone does not address how individuals may continue to process and react to negatively valenced material that is attended to in a judgmental way. To the extent that ACT complements ABM, it may primarily do so through its emphasis on mindfulness. In short, individuals who receive both ABM and ACT may be less likely to (1) even be aware of stimuli and events that might otherwise trigger rumination and (2) to be more accepting of that which is still noticed. Studies have found that both ABM and mindfulness-based treatments (of which ACT is an example) may cause neuroplastic changes in the brain regions associated with attention, emotion and self-awareness [24, 36–39]. The changes that ABM might bring forward could predict a boost to ACT treatment.

Another lens through which ABM and ACT could be seen as complementing each other entails multilevels of cognitive processing. ABM could be thought to involve “lower-order” cognitive processes incorporating implicit attention without the involvement of apparent language or cultural-based processes. ACT, on the other hand, implicates more “higher-order” cognitive processes. Somewhat relatedly, Skinner’s distinction between contingency-shaped (ABM) and rule-governed behavior (ACT) [40] may also be useful in considering how ABM and ACT could work together. ABM targets contingency-shaped behavior. In the dot-probe paradigm attention under the discriminative control of positive stimuli is shaped to establish a positive bias. Once established at sufficient strength, selective attending may be maintained by its naturally reinforcing consequences. In contrast to ABM, ACT is more concerned with rule-governed behavior. Mindfulness instruction and practices in ACT can be viewed as efforts to increase attentional flexibility by bringing certain facets of present moment awareness under more deliberate control. However, unlike in ABM, the agenda is less on shifting from *what* is attended to, to that of altering *how* whatever is noticed is attended to in a less judgmental and more accepting manner.

### Hypotheses

This study has the following hypothesis;Group-based ACT will reduce residual symptoms of depression when compared to patients not receiving group-based ACTGroup-based ACT will reduce cognitive, neurobiological, and emotional markers of vulnerability in a sample of patients in remission from depression when compared to patients not receiving group-based ACTGroup-based ACT preceded by ABM will have greater effect on reduction of residual symptoms than group-based ACT proceeded by sham ABMThe absolute and relative reductions in episodes of low-mood among those receiving group-based ACT will be maintained over a 12-month follow-up periodIncreased valued living and mindfulness skills as well as decreased scores on perceived stress, experiential avoidance, automatic thoughts and cognitive fusion, alone or in combination, will significantly mediate reductions in depressive symptoms in group-based ACT

## Methods/design

### Overview of study design

Figure 2 illustrates the design of the study. Former depressed participants and those in remission (*n* = 220) will initially be randomized in Phase 1 to receive either ABM or a control condition without bias modification. All participants recruited at Sørlandet (*n* = 120), half of whom will have just received ABM, will next receive an 8-week, group-based ACT intervention. The dependent variables are residual symptoms of depression, cognitive, neurobiological, and emotional markers of vulnerability, as well as frequency of major depressive episodes over a 12-month follow-up. The SPIRIT (Standard Protocol Items: Recommendations for Interventional Trials) for this research is available in Additional file 1.

**Fig. 2 Fig2:**
[figure not shown]
Overview of study design

### Participants

Participants with a history of major depression will be recruited by referrals. While referrals are accepted from any source, the majority are expected to come from local hospitals, regular general practitioners, and self-referrals. The age of the participants will range from 18 to 65 years. Diagnostic assessment and evaluation of remission will be made in accordance with the structured clinical interviews for *Diagnostic and Statistical Manual of Mental Disorders, 4th edition* (*DSM-IV*) criteria (The Mini International Neuropsychiatric Interview (MINI)) [41].

#### Inclusion criteria

Inclusion criteria are as follows:Participants with a history of major depression, currently in remissionAged between 18 and 65 years

#### Exclusion criteria

Current or past neurological illnessBipolar disorderPsychosisDrug addictionAttention deficit disorder with and without hyperactivity (ADHD and ADD)

### Sample size and power

An earlier preliminary study using the same ABM procedure [13] found a relatively high effect on the measure of residual symptoms (Hedges’ *g* = 1.32). Based on former group-based ACT interventions, we expect an effect above *d* = 0.50 on measures of residual symptoms [42]. We have no relevant studies that can guide our expectations when it comes to the sequential combination of ABM and ACT compared to ACT alone. However, we hypothesize that the combination should result in a larger effect than the individual interventions. Statistical power analysis using G*Power [43] indicates that with an α-level at 0.05 and, a β-level at 0.10, the total sample size in a design like this should be 206 to detect differences in the main and interaction effects of a moderate to medium effect size, *f* = 0.25, with a one-two-way analysis of variance (ANOVA). We plan to recruit 220 participants in total, which allows for some attrition before the power will be reduced.

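### The sample size of 206 fits only a 2-df test that the ABM by ACT layout does not contain, and one f = 0.25 hides how power differs between the main effects, the interaction and hypothesis 3

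*Protocol article*

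**What the plan says.** The Sample size and power section of the protocol article gives one calculation, "with an α-level at 0.05 and, a β-level at 0.10", and concludes that "the total sample size in a design like this should be 206 to detect differences in the main and interaction effects of a moderate to" mid-range size, f = 0.25, "with a one-two-way analysis of variance (ANOVA". It plans 220 participants and says that this leaves room for some attrition. Numerator degrees of freedom and number of groups are not printed.

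The same section says of ACT: "Based on former group-based ACT interventions, we expect an effect above *d* = 0.50 on measures of residual symptoms". It gives no expected size for ABM plus ACT against ACT alone, and states that no relevant study guides that expectation.

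The layout is in Overview of study design. All 220 are randomised to ABM or control, and then "All participants recruited at Sørlandet (*n* = 120), half of whom will have just received ABM", go on to group ACT; the remaining 100 do not. The Abstract gives the aim as finding out whether "the effect of group-based ACT on reducing residual depressive symptoms can be enhanced by preceding it with ABM". Hypothesis 3 compares ACT after ABM with ACT after sham ABM.

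**The concern.** Two things do not fit.

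- **The number.** Both factors have two levels, so each main effect and the interaction has 1 df. A single N for all three should be the 1-df N, and 206 is not that number. The room for attrition (220 against 206) rests on it.
- **The effect size.** Cohen's f is applied equally to main and interaction effects, but on the outcome scale the same f is twice as large a quantity for a 2x2 interaction as for a two-group main effect. A reader who sees 90% power for moderate effects cannot tell this. Hypothesis 3, read as a comparison among ACT recipients, uses only 120 people, so a figure for the whole sample does not describe it.

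At stake is how a null result on enhancement is read, and how much loss to follow-up the trial can bear at the stated power.

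**Working it through.** **Inputs.** Alpha 0.05, power 0.90, f = 0.25, N = 220 (Sample size and power). Cells with ACT 60/60 (Randomizing and treatment allocation). Cells without ACT 50/50: assumed, 220 − 120 = 100 split equally. Observations independent, no attrition, unadjusted ANOVA.

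**1. Reproducing 206.** Noncentral F with λ = N f², denominator df = N − number of groups; smallest N with power of at least 0.90:

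| Numerator df | N needed | Power at 206 | Power at 220 |
|---|---|---|---|
| 1 | 171 | 94.6% | 95.8% |
| 2 | 206 | 90.1% | 92.0% |
| 3 (four cells, one-way) | 231 | 86.0% | 88.4% |
| 4 | 252 | 82.3% | 85.1% |
| 5 | 270 | 78.9% | 82.0% |

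The 206 appears exactly at 2 df, whether 3, 4, 6, 8 or 12 groups are assumed, and at no other df from 1 to 5. Changing the printed inputs gives near misses only: 1 df with 95% power gives 210, and 1 df with alpha 0.025 gives 202.

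**2. Attrition margin.** From 206: 220 − 206 = 14, or 14/220 = 6.4%. From the 1-df N: 220 − 171 = 49, or 49/220 = 22.3%. For a four-cell one-way test there is no margin: 231 − 220 = 11 short.

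**3. What f = 0.25 means.** Two equal groups: f = d/2, so d = 0.50. Balanced 2x2 interaction with difference of differences D: f = D/(4 SD), so D = 4 × 0.25 = 1.0 SD. If ACT were worth 0.5 SD after sham, f = 0.25 would require 0.5 + 1.0 = 1.5 SD after ABM.

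**4. Interaction power, cells 60/60/50/50.** SE = √(1/60 + 1/60 + 1/50 + 1/50) = √0.0733 = 0.271 SD; λ = (D/SE)²; denominator df 216.

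| D | λ | Power |
|---|---|---|
| 0.25 SD | 0.85 | 15% |
| 0.5 SD | 3.41 | 45% |
| 0.75 SD | 7.67 | 79% |
| 1.0 SD | 13.64 | 96% |

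90% power is reached at D = (1.960 + 1.282) × 0.271 = 0.88 SD. With 55 per cell, the power figures change by less than one point.

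**5. Hypothesis 3 as 60 v 60.** SE = √(2/60) = 0.183 SD. At d = 0.5: 0.5/0.183 − 1.960 = 0.78, so power is about 78% (77.5% by noncentral F). 90% power needs d = 3.242 × 0.183 = 0.59, about 0.6. Put differently, d = 0.50 is f = 0.25 with 1 df, which needs 171 people, and this contrast has 120.

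**6. Baseline adjustment.** Replacing SD by SD√(1 − r²) for assumed baseline correlations r of 0.3, 0.5 and 0.7, interaction power at D = 0.5 SD becomes about 49%, 57% and 73%.

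**The case against.** The strongest defence is that the power sentence is true on its own metric. At f = 0.25 each 1-df effect, the interaction included, has about 96% power at 220 and about 95% at 206. This stands. A reader might infer from the table above that the claim of 90% for the interaction is false; it is not. It is stated in a unit that conceals how large the effect must be.

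A reader might also infer that the trial has only 45% power for its central question. The document does not support that. The 0.5 SD interaction is a benchmark borrowed from the expected ACT effect, and the protocol sets none. The figure is for an unadjusted ANOVA, whereas Data analysis plans mixed models and the outcome is measured at six assessments. Hypothesis 3 is also most directly read as the 60 v 60 contrast, not as a difference of differences; the Abstract's wording about enhancing the ACT effect is the main support for the interaction. So 45% is one point in a range.

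Finally, the df mismatch does no harm to the 1-df tests, since 206 exceeds 171, and the origin of the 206 in a 2-df calculation is inferred because the software settings are not printed. Both are fair. What remains is that the printed N matches no test in the described layout at the printed inputs, and that the 60 v 60 contrast falls short of 90% at d = 0.5.

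**Conclusion.** The point holds as a misstated sample-size paragraph, not as proof that the trial is too small. The 206 is a 2-df figure in a design whose main and interaction effects have 1 df (171) and whose four-cell one-way test has 3 df (231). The margin against 220 is therefore understated for the 1-df tests and absent for the one-way test. The shared f = 0.25 stands for d = 0.50 in one place and 1.0 SD in another, and the total-sample 90% does not transfer to hypothesis 3 as a comparison of 120 people, where power is about 78% at d = 0.5.

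These figures assume independence, full retention, two-sided alpha 0.05, no baseline adjustment and an equal split of the 100 without ACT. Adjustment would raise power. ACT is given in groups of 8–12, so any positive within-group correlation would lower it.

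**What to change.** Rewrite the power paragraph by effect, stating that the figures assume independent observations, no attrition and an unadjusted ANOVA:

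1. Main effect, 1 df, d = 0.50: 171 needed for 90% power; about 96% at 220.
2. Hypothesis 3 as ABM+ACT versus sham+ACT, 60 v 60: about 78% at d = 0.5; 90% only at about d = 0.6.
3. ABM by ACT interaction, cells assumed 60/60/50/50: 90% only for a difference of differences of about 0.88 SD; 15%, 45%, 79% and 96% for 0.25, 0.5, 0.75 and 1.0 SD. Say that the protocol sets no expected size and that baseline adjustment would raise these figures.

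Name the test and its degrees of freedom in place of the unclear one-/two-way wording, and recompute the attrition margin from the corrected N.

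The cost is one reworded paragraph, with no added participants or data. The downside is a less favourable stated power for the enhancement question.

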### Procedures

#### Randomizing and treatment allocation

Following enrollment in Phase 1 and randomization into experimental versus control conditions, tasks (ABM or control) will be completed twice daily over the course of 14 days; i.e., 28 sessions total (see Browning et al., [13] and Fig. 4). Allocation to treatment condition will be done using random-number-generator function in Microsoft Excel by individuals not involved in the recruitment, assessment, treatment, or follow-up of patients. Figure 3 shows the Standard Protocol Items: Recommendations for Interventional Trials (SPIRIT) Figure for the trial process.

Data will be collected in six assessment sessions: (1) immediately before starting Phase 1, (2) immediately after completion of Phase 1, and then at (3) 1 month, (4) 2 months, (5) 6 months, and finally (6) 12 months following Phase 1. The effect of Phase 1 on attentional bias (measured with the dot probe) as a manipulation check will be assessed on the second visit. Participants after Phase 1 (*n* = 120) will receive an 8-week-long ACT-based group intervention. Half of these participants (*n* = 60) will have received ABM during the task phase, while the remainder will be from the control condition Fig. 3.

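### The only power statement (206 needed, 220 planned, 90% power) does not cover ABM+ACT versus sham ABM+ACT, which rests on 60 v 60 and has about 78% power at the same effect size

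*Protocol article*

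**What the plan says.** The aim in the Abstract is to "investigate if the effect of group-based ACT on reducing residual depressive symptoms can be enhanced by preceding it with ABM". The closing paragraph of the Background repeats it, and the third item under Hypotheses sets ACT after ABM against ACT after sham ABM, with residual symptoms as the outcome.

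Under Sample size and power, the calculation is that "with an α-level at 0.05 and, a β-level at 0.10, the total sample size in a design like this should be 206", in order "to detect differences in the main and interaction effects of a moderate to medium effect size", f = 0.25, by ANOVA. Numerator degrees of freedom and number of groups are not given. The paragraph ends: "We plan to recruit 220 participants in total, which allows for some attrition before the power will be reduced". It also concedes: "We have no relevant studies that can guide our expectations when it comes to the sequential combination of ABM and ACT compared to ACT alone".

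Under Overview of study design: "All participants recruited at Sørlandet (*n* = 120), half of whom will have just received ABM, will next receive an 8-week, group-based ACT intervention". Under Randomizing and treatment allocation, half of these (n = 60) "will have received ABM during the task phase, while the remainder will be from the control condition".

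The section gives no separate power figure for the 120, and no attrition rate.

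**The concern.** The comparison that answers the stated aim can use only people who received ACT. There are 120 of them, fewer than the 206 that the paragraph says are needed. The remaining 220 − 120 = 100 participants receive ABM or the control task without ACT, so they carry no information on ABM+ACT versus sham ABM+ACT. The margin of 220 − 206 = 14 participants does not exist for this contrast either.

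A reader of the sample-size paragraph would take the central question to have 90% power with room for dropout. A non-significant result on the third hypothesis could then be read as stronger evidence that ABM adds nothing to ACT than the design can supply.

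**Working it through.** **Inputs.** From Sample size and power: α = 0.05, β = 0.10, f = 0.25, N = 206 needed, 220 planned. From Overview of study design and Randomizing and treatment allocation: 120 ACT recipients, 60 per arm.

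**Step 1: reproduce 206.** For a fixed-effects ANOVA, power = P(F′ > F_crit), where F′ is noncentral F with df1 numerator and N − g denominator degrees of freedom and noncentrality λ = N·f².

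| df1 | smallest N for 90% power |
|---|---|
| 1 | 171 |
| 2 | 206 |
| 3 | 231 |

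The number of groups g (2, 3, 4 or 6) does not change these. With df1 = 2, N = 206 gives λ = 206 × 0.0625 = 12.875 and power 90.1%; N = 205 gives 89.9%; N = 220 gives 92.0%. So 206 is a correct answer to a two-degree-of-freedom question. The third hypothesis is a one-degree-of-freedom contrast, for which the like-for-like requirement is 171.

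**Step 2: power for the third hypothesis.** Two equal groups, so d = 2f = 0.50 and df1 = 1.

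- λ = 120 × 0.25² = 7.5 on 1 and 118 degrees of freedom; F_crit = 3.92; power = 77.5%.
- Equivalent two-sided t test: noncentrality = 0.50 × √(60/2) = 2.739; critical value 1.980; power = 77.5%. The normal approximation gives 78.2%.
- Type II error = 1 − 0.775 = 22.5%, against the stated 10%.

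**Step 3: what 90% power would take.**

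- At d = 0.50: 171 ACT recipients in total (170 by normal approximation). The shortfall is 171 − 120 = 51.
- At 60 v 60: smallest detectable d = 0.597, about 0.60 (f about 0.30).
- For smaller true effects at 60 v 60, power is 58% at d = 0.40 and 37% at d = 0.30.

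**Step 4: sensitivity.** The article supplies none of the quantities varied here; all are assumptions. Each row changes one thing from the 77.5% case.

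| Assumption | Power at d = 0.50 |
|---|---|
| 10% loss (54 v 54) | 73% |
| 20% loss (48 v 48) | 68% |
| Baseline adjustment, correlation 0.4 (effective d = 0.5/√(1 − 0.16)) | 84% |
| Baseline adjustment, correlation 0.5 | 88% |
| Baseline adjustment, correlation 0.6 | 92% |
| Clustering in ACT groups of 10, ICC 0.01 (design effect 1.09) | 74% |
| Clustering in ACT groups of 10, ICC 0.05 (design effect 1.45) | 61% |

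**Step 5: contrasts that do use all 220.** ACT versus no ACT, 120 v 100 at d = 0.50, has about 96% power. The point does not extend to those hypotheses.

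**The case against.** **The paragraph covers main and interaction effects and never claims 90% power for the third hypothesis in particular.** True as a matter of wording, and no hypothesis is labelled primary; calling this contrast central rests on the aim in the Abstract and Background. But the paragraph is the only power justification in the article, and neither effect it names is this contrast. An ABM main effect over 220 pools people who had no ACT. An ABM-by-ACT interaction asks whether the ABM effect differs with and without ACT. The one-degree-of-freedom interaction at f = 0.25 has about 96% power with 220, but in a balanced two-by-two layout that f means a difference of differences of 1.0 SD. At 0.5 SD (f = 0.125, λ = 220 × 0.015625 = 3.44) power is about 45%.

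**A reader might infer that 206 is wrong, or that the trial falls 86 short (206 − 120).** Neither follows. The figure reproduces, and on the one-degree-of-freedom basis that gives 78% the shortfall is 51.

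**A reader might infer a type II error of up to 32%.** That upper end (1 − 0.68) comes entirely from an assumed 20% loss treated as complete. The article gives no rate, and its mixed models keep participants with some missing observations.

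**The planned analysis is a mixed model over six assessments, so a t-test figure may be pessimistic.** This stands as a limit: 78% is power on the protocol's own ANOVA basis, not of the final model. Baseline adjustment might close most or all of the gap, but that cannot be asserted from the document. It gives no correlation, and the Data analysis section adds covariates only where pre-treatment differences are found. Treatment in groups of 8–12 could pull power the other way, depending on an ICC and on whether the arms are mixed within groups, neither of which is stated.

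**The conventional 80% is close to 78%.** So it is, but the protocol chose 90% and says attrition is covered.

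**Conclusion.** The point holds as a matter of scope, not of arithmetic. The 90% power and the 14-person margin belong to the full Phase 1 sample and do not apply to ABM+ACT versus sham ABM+ACT. At the protocol's own effect size that contrast has about 78% power before attrition.

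This rests on a two-sided test at 0.05, d = 0.50 obtained from f = 0.25 for two equal groups, independent observations, no baseline adjustment and no dropout. The d of 0.50 is itself a generic target, since the protocol says that no prior study guides the size of this effect. The conclusion does not depend on the sensitivity figures: the 206 exceeds the 120 people who can enter the comparison whatever is assumed about dropout, correlation or clustering.

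**What to change.** In Sample size and power:

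1. State for the third hypothesis that 60 v 60 participants contribute, that power is about 78% at d = 0.50 (two-sided 0.05) before attrition, and that the effect detectable with 90% power is d = 0.60.
2. Limit the 206/220 figure and the attrition margin to contrasts that use all 220 participants, and give the numerator degrees of freedom (two reproduces 206).
3. If figures for attrition, baseline adjustment or clustering in ACT groups are added, label each as an assumption with its range, and do not present any of them as the trial's power.

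This rewrites one paragraph. It needs no extra enrolment and no change to design or analysis. The cost is a less favourable stated power for the central question.
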